**2a) Trial registration:**

EudraCT: 2017-004732-11

ISRCTN 16774163

**2b) Trial registration Data Set:**

1. Primary registry and trial identifying number: ISRCTN 16774163

2. Date of registration in primary registry: 10^th^ May 2018

3. Secondary identifying numbers: EudraCT: 2017-004732-11

4. Sources of monetary support: Meningitis Research Foundation

NHS National Institute of Health Research

Oxford Biomedical Research Centre.

5. Primary sponsor: University of Oxford

6. Secondary sponsor: N/A

7. Contact for public enquiries: [name]

Oxford Vaccine Group

Churchill Hospital

[name]

[name]

[[contact]](mailto:[contact])

8. Contact for scientific enquiries: [name]

Oxford Vaccine Group

Churchill Hospital

[name]

[name]

[[contact]](mailto:[contact])

9. Public title: Meningococcal B Booster vaccine in young

people.

10: Scientific title: Preventing meningitis in young people after

infant immunisation: effect of a single

meningococcal 4CMenB vaccine booster over

10 years of age.

11. Countries of recruitment: United Kingdom

12. Health condition(s) or problem(s) studied: Capsular group B meningococcal vaccination

Capsular group B meningococcal vaccine immunogenicity

13. Intervention(s):

Intervention name: 4CMenB (Bexsero^®^ –GSK, Rixensart, Belgium)

Intervention description:

Previously immunised children:

Group 1-6: 4CMenB given on day 0. Blood tests at Day 0, 28, 180 and 365.

Naïve children:

Group 7: 4CMenB given on day 0 and 365. Blood tests at Day 0, 28, 180 and 365.

Group 8: 4CMenB given on day 0 and 28. Blood tests at Day 0, 28, 180 and 365.

14. Key inclusion and exclusion criteria:

Inclusion criteria:

For recruitment to study groups 1 to 6 only

- Healthy children aged approximately 11 years who have completed a vaccination course of 4CMenB as an infant or toddler in clinical trials V72P6, V72P6E1, V72P9 or V72P9E1.

For recruitment to Naïve groups 7 and 8 only

- Healthy children aged approximately 11 years who have not previously received 4CMenB vaccine.

Exclusion criteria:

All groups

- History of invasive meningococcal B disease.
- History of being a household contact with a case of confirmed meningococcal meningitis
- Confirmed or suspected immunodeficiency.
- A family history of congenital or hereditary immunodeficiency, or maternal HIV.
- History of anaphylactic reaction to any component of the vaccine.
- Any other significant disease or disorder which, in the opinion of the Investigator, may either put the participants at risk because of participation in the trial, or may influence the result of the trial, or the participant’s ability to participate in the trial.
- Thrombocytopenia or any bleeding disorder.
- Receipt of blood, blood products, or plasma derivatives within the past 3 months.

Exclusion to study groups 1 to 6 only

- Any previous vaccination with 4CMenB or another MenB vaccine except as part of V72P6, V72P6E1, V72P9 or V72P9E1 clinical trials.
- Receipt of immunosuppressive therapy such as anti-cancer chemotherapy or radiation therapy within the preceding 1 month or long-term systemic corticosteroid therapy.

Exclusion to Naïve groups 7 and 8 only

- Previous vaccination with 4CMenB vaccine or with any other meningococcal B vaccine.
- Receipt of immunosuppressive therapy such as anti-cancer chemotherapy or radiation therapy.
- Current receipt of long-term systemic corticosteroid therapy.
- Long term prophylactic antibiotic use.

15. Study type: An open-label, exploratory immunogenicity study.

16. Date of first enrolment: 24^th^ March 2018

17: Sample size: Target = 113 participants; 83 previously immunised

(anticipated 50% enrolment in this group) and 30 naïve.

Currently enrolled = 40 previously immunised, 12 naïve.

18. Recruitment status: Actively recruiting.

19. Primary outcome:

Serum bactericidal activity against meningococcal strains at day 0 and 180 days post-immunisation, measured by validated assay.

20. Key secondary outcomes:

- Serum bactericidal activity before vaccination, measured at day 0.
- Serum bactericidal activity against meningococcal strains. Quantification and qualitative characterisation of B-cell memory and other immune cell types, measured at day 0, 28, 180 and 365 post-immunisation.
- Parental recording of eDiary information including axillary temperature check at 6 hours post vaccination. Reactogenicity data gathered for 7 days after any vaccines given.

21: Ethics review:

This trial has been approved by Nottingham 2 Research Ethics Committee (reference 17/EM/0466).

22: Completion date: Expected completion date March 2020 (24 month trial

period).

23: Summary results: Not yet available.

24: IPD sharing statement:

The results, interpretation and conclusions will be disseminated to parents and participants via letter and will be submitted for publication in peer-reviewed journals. The findings of this study could also be used to inform vaccination policy in the U.K.

**3) Protocol version:**

Protocol version 4.0 dated 21^st^ June 2018

Revision chronology

**Original:** Protocol version 1.0 dated 20^th^ November 2017.

**First amendment:** Protocol version 2.0 dated 30^th^ January 2018. Addition of the option to return a reply slip for previously vaccinated participants when indicating whether they would like to take part in this study. Changing the randomisation of participants in the naïve group from a computer-based system (Sortition) to a paper envelope-based system to avoid issues with internet access within participants’ homes.

**Second amendment:** Protocol version 3.0 dated 19^th^ March 2018. Amendment of the protocol and parent and assenting information booklets to change the use of a continuous temperature monitoring system to being optional. Addition of reply slips for the general practitioner (GP) and Child Health Information Service (CHIS) so that they can notify us if they have managed to forward an information pack to a family. Amended typographical errors in group card 7 and 8, study labels and the assenting information booklet for non-naives.

**Third amendment:** Protocol version 4.0 dated 21^st^ June 2018. Changing of the statistical analysis section to include a descriptive analysis of immunogenicity at 180 days, and changes to the wording of how the analysis will be done. Changing of the wording of the exclusion criteria from “household contact of bacterial meningitis” to specify “meningococcal meningitis”. Updated the patient information leaflet to change the details of where to opt-out of receiving information on future trials via mail and to update according to the General Data Protection Regulation (GDPR).

**4) Funding:**

The study is part funded through a research grant from the Meningitis Research Foundation (MRF), project 1702.0 (study groups 5 to 8) and part funded through a research grant from the NHS National Institute of Health Research Oxford Biomedical Research Centre.

**5c) Role of sponsor and funders:**

The University of Oxford provided guidance regarding study design, but play no role regarding the collection, management, analysis and interpretation of data.

MRF and NHS National Institute of Health Research Oxford Biomedical Research Centre play no role in the design and implementation of this project.

**5d) Overseeing groups:**

The University of Oxford Trials Safety Group (TSG) will conduct a review of all SAEs for the trial reported during the quarter and cumulatively. The aims of this committee include:

- To pick up any trends, such as increases in un/expected events, and take appropriate action.
- To seek additional advice or information from investigators where required.
- To evaluate the risk of the trial continuing and take appropriate action where necessary.

**Introduction:**

**6a) Background and rationale:**

Despite the existence of effective antibiotics and recent advances in vaccinology, meningococcal disease remains firmly in the public eye. Of the main *Neisseria meningitidis* capsular groups which cause disease in humans, group B meningococcus (MenB) has the highest incidence in the U.K.(1) and has proved most difficult to tackle through the design of an effective vaccine. Concerns about a capsular group B meningococal vaccine based on the polysaccharide capsule inducing poor immunogenicity and possibly eliciting a harmful autoimmune response(2) led to the development of an alternative approach using subcapsular proteins. The four components of 4CMenB consist of subcapsular antigens and outer-membrane vesicles, including a recombinant factor H binding protein (fHbp), *Neisseria meningitidis capsular* group B neisserial heparin binding antigen (NHBA) fusion protein, recombinant *Neisseria meningitidis* group B neisserial adhesin A (NadA) protein and outer membrane vesicles (OMV) from *Neisseria meningitidis* group B strain NZ98/254 containing PorA P1.4.

4CMenB was licensed in 2013 and introduced into the UK routine vaccination schedule in September 2015 for infants in a 2+1 schedule (primary series at two and four months, booster dose at 12 months of age). The cost-effectiveness of infant vaccination was borderline, despite this age group suffering the highest rate of disease. Furthermore, an adolescent programme was not initiated in the UK due to the relatively lower rate of disease in this age group and uncertainty over the duration of protection in this age group and the potential for induction of wider herd protection(3). Even when the best-case scenarios of strain coverage (88%), vaccine efficacy (95%), duration of protection (120 months), and the capacity to elicit 30% protection against acquisition of carriage were considered, an adolescent programme was estimated to not be cost-effective at the list price for the vaccine.

However, adolescents are responsible for the majority of nasopharyngeal carriage of meningococcus(4) and the majority of transmission. They also suffer from the second highest incidence rate of invasive meningococcal disease (IMD) of any age group(5). Investing in an adolescent MenB booster programme will not only reduce incident cases, but also may interrupt transmission of hyperinvasive MenB strains, thus reducing overall disease burden.

In 2006, the first infants were vaccinated against MenB in a trial in Oxford as part of 4CMenB clinical development(6) and received 4CMenB at two, four, six, and 12 months of age. After three doses, human serum bactericidal assay (SBA) analysis showed that 4CMenB was immunogenic against strains expressing homologous NadA, fHbp and PorA. A recall response was induced after the fourth dose at 12 months of age. Some of these children were then recruited to participate in a follow-up study, aiming to investigate the persistence of the SBA response, and the response induced by a toddler booster injection given at 40 months of age(7). This showed that the booster dose in the 4CMenB-primed participants generated greater increases in SBA titers than in naïve children who were receiving their first ever dose at 40 months of age. These results suggest that a memory B-cell response, induced by 4CMenB received in infancy, was present and supported a recall response two years later. From the children who took part in the first study (vaccinations received under 12 months of age), some received a boost at 40 months and some did not.

4CMenB has also been evaluated in naïve adolescents, and it was demonstrated that two doses induced robust immune responses against the vaccine antigens, including bactericidal activity (SBA)(8-10). The vaccine was well tolerated, and no safety concerns were identified(11). 4CMenB is currently licensed for adolescent use, with naïve adolescents requiring two injections at a minimum 1-month interval. However, a possible booster immune response in adolescents after infant vaccination with 4CMenB has not yet been evaluated or compared with that of naïve adolescents.

While the level of vaccine-induced protective antibody titres against MenB more than ten years after the last vaccination is expected to be low, previously immunised adolescents may have a substantial level of vaccine-specific memory B-cells. This may in turn produce a strong antibody recall response to a new encounter with the antigen in the form of a booster vaccine. If this was the case, a single dose adolescent booster could be envisaged as an addition to the current vaccination schedule. Information that will arise from U.K.-based adolescent carriage studies that are currently being carried out by the Department of Health will also help to inform this decision.

**7) Objectives:**

Children who took part in previous 4CMenB trials are now approaching adolescence, and therefore we are presented with the unique possibility to specifically address the following questions:

1. What is the persistence of the protective antibody response and B-cell memory in adolescents 10 years after infant vaccination?
2. What is the persistence of protective antibody responses and B-cell memory among adolescents after infant vaccination with toddler boosting (eight years after the last 4CMenB vaccination)?
3. Is the protective antibody response to an adolescent booster among individuals immunised in early childhood higher and/or more persistent than in naïve adolescents?

Analysis of bactericidal activity (primary outcome).

The ability of the antibodies in participants’ serum samples to mediate killing of meningococci in the presence of complement (serum bactericidal activity (SBA)), will be quantified. The target strains in the SBA assay will be a panel of wild-type strains, in order to elucidate the antigen-specific SBA titre. The SBA titre will be calculated as the lowest concentration of the serum dilution giving a 50% reduction of colony forming units (CFUs) of a specified inoculum of bacteria after incubation with participant serum in the presence of complement.

Cellular responses and cytokine release (exploratory outcome).

Laboratory analyses to quantify the B- and T-cell responses specific to 4CMenB may be performed when feasible using peripheral blood mononuclear cells (PBMCs) and plasma derived from study participants sampled before, and after each vaccine dose, using the assays described below:

- Analyses of B cell responses: The ability of 4CMenB to stimulate a detectable increase in IgG, IgA and IgM producing antigen-specific memory B cells enumerated by ELISPOT using plates coated with vaccine antigens (OMVs, fHbp, NHBA, NadA and/or PorA). The phenotype and kinetics of the B-cell subsets involved in the response can be determined by flow cytometry. In addition, other assays to monitor the B-cell immune response to the vaccines may be performed if sufficient samples are available.

- Analyses of T cell responses and cytokine release: In order to explore the ability of 4CMenB to stimulate T cell responses, we aim to quantify (when possible) vaccine-induced responding T-cells by proliferation or production of cytokines upon stimulation of PBMCs with meningococcal vaccine antigens after immunisation, as compared to pre- immunisation (by ELISPOT or intra-cellular cytokine assays). The phenotype of the responding effector and memory T-cells subsets can be characterised by flow cytometry and intra-cellular cytokine assay when possible. Moreover, other assays to monitor the T-cell immune response and cytokine release to the vaccines may be performed if sufficient samples are available.

- Serum antibody reactivity with human factor H (FH): Binding of serum IgG and IgM antibodies to human FH may be measured by ELISA, performed as described in previous studies(12). If serum anti-FH reactivity is detected, recombinant specific human FH domains can be used to determine the location of the FH epitopes reactive with the antibody. If detected, further exploratory assays will be performed to characterise the function and persistence anti-FH antibody.

**8) Trial design:**

An open-label exploratory immunogenicity analysis.

**SPIRIT figure for study timeline:**

**
[figure not shown]
**

**9) Study setting:**

Study visits will take place in clinics at the local tertiary level hospital, or in the homes of participants. The site will depend upon several factors including participant preference and distance from the study centre. A list of study sites is below:

- John Radcliffe Hospital, Oxford.
- Participant homes across Oxfordshire, Berkshire, Buckinghamshire and neighbouring counties.

**10) Eligibility criteria:**

Key inclusion and exclusion criteria:

Inclusion Criteria for recruitment to all study groups:

- Parents willing and able to comply with trial protocol requirements.
- Parents have given informed consent.
- Participant is willing and able to give informed assent.

For recruitment to study groups 1 to 6 only

- Healthy children who have taken part in clinical trials V72P6, V72P6E1, V72P9 or V72P9E1.

For recruitment to Naïve groups 7 and 8 only

- Healthy children age-matched with groups 1-6 who have not previously received 4CMenB.

Exclusion Criteria

- Children of parents who are on the delegation log for this study.
- History of invasive meningococcal B disease.
- Household contact with a case of confirmed meningococcal meningitis.
- Confirmed or suspected immunodeficiency.
- A family history of congenital or hereditary immunodeficiency, or maternal HIV.
- History of anaphylactic reaction to any component of the vaccine.
- Any other significant disease or disorder which, in the opinion of the Investigator, may either put the participants at risk because of participation in the trial, or may influence the result of the trial, or the participant’s ability to participate in the trial.
- Participants who have participated in another research trial involving an investigational product in the past 12 weeks.
- Prior or planned receipt of any other investigational vaccine or drug.
- Thrombocytopenia or any bleeding disorder.
- Receipt of blood, blood products, or plasma derivatives within the past 3 months.

Exclusion to study groups 1 to 6 only

- Any previous vaccination with 4CMenB vaccine except as part of V72P6, V72P6E1, V72P9 or V72P9E1 clinical trials.
- Any previous vaccination with another meningococcal B vaccine.
- Receipt of immunosuppressive therapy (anti-cancer chemotherapy or radiation therapy) within the preceding 1 month or long-term systemic corticosteroid therapy (e.g. oral prednisolone >0.5ml/kg/day or intravenous glucocorticoid steroid). Nasal, topical or inhaled steroids are allowed.

Exclusion to Naïve groups 7 and 8 only

- Previous vaccination with 4CMenB vaccine or with any other meningococcal B vaccine.
- Receipt of immunosuppressive therapy (anti-cancer chemotherapy or radiation therapy).
- Current receipt of long-term systemic corticosteroid therapy (e.g. oral prednisolone >0.5ml/kg/day or intravenous glucocorticoid steroid). Nasal, topical or inhaled steroids are allowed.
- Long term prophylactic antibiotic use.

**11a) Interventions for each group:**

All participants will be required to undergo four episodes of venepuncture as part of the immunogenicity analysis. All naïve participants (groups 7 and 8) will receive two doses of 4CMenB either on day 0 and 28 or day 0 and 365. All follow-on participants (groups 1-6) will receive one dose of 4CMenB on day 0.

**11b) Criteria for discontinuing or modifying allocated interventions:**

N/A

**11c) Strategies to improve adherence to intervention protocols:**

Strategies include home visits and the use of anaesthetic cream prior to venepuncture.

**11d) Relevant concomitant care and interventions permitted:**

The only restrictions are listed in the exclusion criteria.

**12) Outcomes:**

Primary outcome:

Serum bactericidal activity against meningococcal strains at day 0 and 180 days post-immunisation, measured by validated assay.

Key secondary outcomes:

- Serum bactericidal activity before vaccination, measured at day 0.
- Serum bactericidal activity against meningococcal strains. Quantification and qualitative characterisation of B-cell memory and other immune cell types, measured at day 0, 28, 180 and 365 post-immunisation.
- Parental recording of eDiary information for 7 days post vaccination. Reactogenicity data gathered at all time points after vaccines given.

**13) Participant timeline:**

[figure not shown]

**14) Sample size:**

This is a preliminary study to explore the persistence and potential impact of antigen-specific memory B cell responses on an adolescent programme, therefore a formal sample size calculation was not carried out and the decision of the sample size in groups 7 and 8 was purely pragmatic. The sample size of the participants in groups 1 to 6 is determined by the number of participants who completed the previous studies in 2006-2009 at Oxford. We anticipate approximately 50% of the 83 previously immunised participants to return to take part in the upcoming study however we aim to recruit as many as possible to improve statistical power.

**15) Recruitment:**

Recruitment, approach and initial eligibility assessment of potential study participants:

Recruitment will take place in geographical areas where appropriate approvals have been granted.

Recruitment to groups 1 to 6 only (previously vaccinated)

Parents/legal guardians of potential participants who previously consented to be contacted regarding future vaccine research will be informed of the study by mailing out and/or emailing invitation letters with the parent and child study information booklets, reply slip, and stamped, addressed envelope. The contact details provided to the Oxford Vaccine Group while participating in clinical trials V72P6, V72P6E1, V72P9 or V72P9E1 will be used.

Recruitment to groups 7 and 8 only (naïve)

Parents/legal guardians of potential participants will be informed of the study through website-based advertising, social media, contacting families registered with the OVG research database, and poster advertisements. Dissemination of the study information booklets, including at GP practices, in educational/recreational settings, mail outs/emails from Child Health Information Service or schools and school newsletters may also be employed.

**16a) Allocation sequence generation:**

Participants in study groups 1 to 6 will not be randomised. The study group to which they are assigned is determined by the previous vaccination course of 4CMenB they received while participating in studies V72P6, V72P6E1, V72P9 or V72P9E1, and they will all receive the same study interventions at the same time points.

Naïve group participants will be randomised to Groups 7 or 8 with an allocation ratio of 1:1. This will be achieved by the use of a randomisation list generated in STATA/IC 14.2.

**16b) Allocation concealment mechanism:**

The randomisation will be implemented using sequentially numbered, opaque, sealed paper envelopes which will be kept in a locked cupboard until the first study visit during which the naïve participant is randomised.

**16c) Implementation:**

The allocation sequence has been generated by the study statistician at the Nuffield Department of Primary Care Health Sciences, University of Oxford. Clinical study staff take the next numbered randomisation envelope to the first study visit. After enrolment the clinical staff member will open the randomisation envelope and unblind the staff and study participant.

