**17a) Blinding:**

This study is unblinded after allocation of groups 7 and 8.

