**20b) Methods for any additional analyses:**

The principal comparisons will be performed on a per-protocol basis where the population for the immunogenicity analysis will consist of all participants who receive one or two doses of the vaccine (depending on the group) and providing at least one evaluable serum sample (after or before vaccination). An intention-to-treat analysis will also be performed where all participants will be included in the analysis if they are successfully vaccinated on Day 0. If a participant later withdraws from the study, data up until that point will be included in the analysis.

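### Envelope opening is tied to enrolment and not placed after the Day 0 vaccination on which the intention-to-treat set depends (minor)

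*Protocol*

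**What the plan says.** **Randomisation and opening.** Section 16b has the envelopes "kept in a locked cupboard until the first study visit during which the naïve participant is randomised". Section 16c adds: "After enrolment the clinical staff member will open the randomisation envelope and unblind the staff and study participant". Section 17a confirms that nothing is masked from then on: "This study is unblinded after allocation of groups 7 and 8".

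**Schedules.** Under section 11a all naïve children "will receive two doses of 4CMenB either on day 0 and 28 or day 0 and 365". Section 2b gives one arm as "Group 7: 4CMenB given on day 0 and 365. Blood tests at Day 0, 28, 180 and 365". Group 8 has the same four blood tests, with its second dose on Day 28.

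**Analysis sets.** Section 20b describes an intention-to-treat analysis in which "all participants will be included in the analysis if they are successfully vaccinated on Day 0". It goes on: "If a participant later withdraws from the study, data up until that point will be included in the analysis". Section 20c rules out imputation. Section 20a makes all statistics descriptive, by group and strain, and takes the fold change in hSBA titre from Day 0 to Day 180 as the primary summary.

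**The concern.** An intention-to-treat set is meant to hold everyone randomised, so that nothing that happens after allocation is known can decide who is counted. Here entry depends on the Day 0 injection, and the protocol allows the allocation to be disclosed before that injection. A family that learns its schedule and leaves, or a child who for any other reason is not vaccinated at that visit, has used up an allocation and is then missing from the set.

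A reason to care about the arm can be found in the protocol. Section 6a says that naïve adolescents need two doses at least a month apart, group 7 waits a year for its second, and section 30 offers no vaccine beyond the trial period. Departure could therefore differ between arms. Nothing is gained by running this risk, because no one needs to know the arm to carry out Day 0. Groups 7 and 8 are also the only randomised part of the study (section 16a).

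**Working it through.** The protocol has no figure of its own to reproduce on this point: section 14 states that no formal sample size calculation was made. The check is mainly a comparison of sections, followed by an illustration of size.

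**Step 1: order of events.**
- Opening: after enrolment, at the first visit (16b, 16c). Its order relative to the Day 0 blood and injection is not stated, and the timeline figures are not reproduced in the text available.
- First visit: section 20a calls Day 180 visit 3. With bloods on Days 0, 28, 180 and 365, visit 1 is Day 0. Any gap between opening and injection therefore lies within one appointment.
- Arms: same dose on Day 0 and same bloods on Days 0 and 28. The first difference is group 8's second dose on Day 28 (2b, 11a).

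**Step 2: who is excluded.**

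| Time of leaving | In the 20b intention-to-treat set? | Day 180 value? |
|---|---|---|
| After opening, before injection | No | No |
| After injection, before Day 28 | Yes, data kept to withdrawal | No |
| Day 28 to before Day 180 | Yes, data kept to withdrawal | No |

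Only the first row is affected by the Day 0 condition.

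**Step 3: illustrative size.** Inputs: 30 naïve children (2b) at 1:1 (16a), taken as 15 per arm. The number of leavers, k, is not given; I assume 1 to 3 in one arm.
- Share of the arm: k/15.
- Half-width of the 95% confidence interval for a log10 mean, in SD units: t(0.975, n−1)/√n with n = 15 − k. At n = 15 it is 0.554.
- Shift of the arm mean if leavers differ from stayers by an assumed 0.5 SD: (k/15) × 0.5.

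| k | n | Share of arm | Half-width (SD) | Ratio to n = 15 | Shift (SD) |
|---|---|---|---|---|---|
| 1 | 14 | 6.7% | 0.577 | 1.04 | 0.03 |
| 2 | 13 | 13.3% | 0.604 | 1.09 | 0.07 |
| 3 | 12 | 20.0% | 0.635 | 1.15 | 0.10 |

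The chance of at least one leaver among 30 is 1 − (1 − p)^30. For an assumed probability p per family of 1%, 2% or 5%, this is 26%, 45% or 79%.

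**Step 4: after the change.** If the envelope is opened only once the injection has been given, the first row of the Step 2 table is empty for newly randomised children: 0 of 15 per arm excluded by the Day 0 condition. The other rows remain.

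**The case against.** The case against giving this much weight is strong, and most of it stands.

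- A reader might infer that the protocol orders disclosure before the injection. It does not; it ties opening to enrolment and leaves the order open. Opening first is the natural reading, but it is a reading.
- The exposure is part of one visit, after the family has been told about the trial and has consented. No departure of this kind is documented.
- A reader might infer that families leaving between Day 0 and Day 28 also fall out of the intention-to-treat set. They do not: they have been vaccinated, and 20b keeps their data up to withdrawal.
- A reader might infer that a planned comparison of group 7 with group 8 is compromised. The analysis is descriptive by group, the group sizes were set pragmatically, and the objectives in section 7 concern persistence and primed versus naïve adolescents. No test between the naïve arms is specified.
- An unvaccinated leaver has no Day 180 value and nothing is imputed, so widening the set's definition alone would recover no primary data. Later opening also leaves families free to act on their allocation before Day 180.
- Opening after the injection would not mask the seven-day diary for dose 1, because parents would still know the arm while completing it.

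What the objection does not remove is the conflict between the label and the rule. The set called intention-to-treat can exclude a randomised child on an event after allocation, and the protocol's sequence allows this without need.

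**Conclusion.** The point holds as a minor one. Section 16c does not place envelope opening after the Day 0 blood and injection, while 20b makes that injection a condition of entry. As written, the set is a modified intention-to-treat set, and a randomised but unvaccinated naïve child is lost from it, possibly in a way that depends on the arm.

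The number affected is unknown and probably small. Each such child is about 6.7% of an arm at an assumed 15 per arm. With one to three losses in one arm, the interval widens by a factor of 1.04 to 1.15. The mean shifts by 0.03 to 0.10 SD if leavers differ by 0.5 SD. These figures rest on assumed losses and an assumed difference, not on anything in the protocol. The documents do not support a claim that the results for groups 7 and 8 are biased.

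**What to change.** **Main change.** State in 16c, with matching words in 16b, that the envelope is opened only after the Day 0 blood sample and vaccination are complete, and that an envelope brought back unopened is logged and returned to the sequence. The Day 0 condition in 20b then excludes no newly randomised child, and no allocation is spent on a child who is never vaccinated. Doses, visits and schedules are unchanged. The cost is a sentence or two and an instruction to staff.

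**Children already randomised.** They keep their allocation. Report by arm any who were randomised but not vaccinated, and label the set modified intention-to-treat. Section 2b lists 12 naïve children enrolled of 30, in an undated entry; if that count is current, 30 − 12 = 18 could still benefit.

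**Optional extension.** Opening at the Day 28 visit, after that blood sample, would also keep the dose 1 diary and the Day 28 data free of knowledge of the arm. It costs families four weeks' notice of their schedule and requires staff to carry vaccine to every naïve Day 28 visit. It is a preference, not a necessity.

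Neither option prevents loss related to allocation between opening and Day 180. Withdrawals in that interval should be reported by arm.
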